#### Data Analysis

For ERP amplitude analysis, electrodes will be grouped according to regions of interest (ROIs). Left prefrontal site: FP1. Left frontal channels: F3, F7. Right prefrontal site: FP2. Midline pre-frontal site: AFz. Midline frontal electrode: Fz. Right frontal channels: F4, F8. Left temporal site: T7. Left central electrode: C3. Midline central electrode: Cz. Right temporal site: T8, Right central electrode: C4. Centro-parietal electrode: CPz. Left parietal sites: P3, P7. Midline-parietal electrode: Pz. Right parietal sites: P4, P8. Midline parieto-occipital electrode: POz. Left occipital site: O1. Right occipital site: O2. Maximum peak time window analysis will be: 100–250 ms for the MMN (Kujala et al., 2007; Paris et al., 2018), 170–230 ms for P200 component (Paulmann et al., 2013), 200 and 350 ms for the P3a (Kujala et al., 2007; Paris et al., 2018), and 400–1,000 ms for the LPP component (Steber et al., 2020).

Event-Related Potentials will be extracted by averaging the data obtained for standard and deviant stimuli, and for each condition independently. The ERPs elicited by standard stimuli will be subtracted from the ERPs elicited by deviants to calculate difference waves. The mean ERPs amplitude will be calculated as follows. For standard stimuli, level of naturalness and group average peak latencies will be determined from all ROIs. Mean amplitudes will be determined by considering a ±50-ms time window centered at the grand mean peak latency. For deviant stimuli, mean amplitudes will be calculated from the difference waves at ROIs. Mean amplitudes will be determined by considering a ±50-ms time window centered to the grand mean peak latency (Kujala et al., 2007; Paris et al., 2018).

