##### EEG assessments

After behavioral assessment at pre- (1st session), mid- (7th session), end- (13rd session), and follow-up sessions (2 and 6 weeks after the end of the intervention), EEG data will be recorded while participants listen to a passive oddball paradigm. Emotional and neutral words uttered by human voices recorded at Stage 1 will be displayed to the participant. During the EEG recording, participants will sit on an armchair while watching a silent movie and will be instructed to pay no attention to the auditive stimuli. One stimulus block containing 1,200 words will be presented for an approximately 20-min paradigm. It will consist of 960 frequently presented neutral-uttered standard stimuli (80%), and occasional 48 anger (4%), 48 disgust (4%), 48 fear (4%), 48 happiness (4%), and 48 sadness (4%) deviant stimuli. Standard and deviant stimuli will be equally uttered with a male, woman, or child voice. The stimuli will be presented pseudo-randomly with deviant stimuli being preceded by at least two standard stimuli. The stimulus sequence will not vary between participants. The stimulus onset asynchrony will be of 1,300 ms. The stimuli will be presented at 60 dB via the Shure SRH1840 audio headset. Autistic participants will be accompanied by their parent if necessary.

Electroencephalographic recording and processing will follow the same methodology as the one described in section “EEG Recording and Processing.”

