##### ERPs

For ERP amplitude analysis, electrodes will be grouped according to ROIs described in section “Data Analysis.” Maximum peak time windows used for data analysis of ERPs will be identical to the one mentioned in section “Data Analysis.” MMN, P200, P3a, LPP will be under study.

Event-Related Potentials will be extracted by averaging the data obtained for standard and deviant stimuli, and for each condition independently. The ERPs elicited by standard stimuli will be subtracted from the ERPs elicited by deviants to calculate difference waves. The mean ERP amplitude will be calculated as follows. For standard stimuli, group and assessment session average peak latencies will be determined from all ROIs for TD and ASD separately. Mean amplitudes will be determined by considering a ±50-ms time window centered to the grand mean peak latency. For deviant stimuli, mean amplitudes will be calculated from the difference waves at ROIs. Mean amplitudes will be determined by considering a ±50-ms time window centered to the grand mean peak latency (Kujala et al., 2007; Paris et al., 2018).

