##### Statistical analysis on ERPs data

The statistical significance of ERP components will be tested by comparing their mean amplitudes to zero at ROIs using one-sample *t*-tests. This method will allow us to focus exclusively on significant responses, and to distinguish significant scalp distributions from noise. Statistically significant ERPs will be considered for further amplitude analysis.

Group comparisons will be conducted by Group × ROI repeated measures ANOVAs on each ERP and assessment session separately, for standard stimuli. Similarly, for deviant stimuli, Group × ROI × Deviant repeated measures ANOVAs will be performed.

For standard stimuli, time comparisons will be conducted by Assessment Session × ROI repeated measures ANOVAs on each ERP and group separately. For deviant stimuli, Assessment Session × ROI × Deviant repeated measures ANOVAs will be performed.

Scalp distribution comparisons for standard stimuli will be assessed by Group × Laterality (FP1, F3, F7, T7, C3, P3, P7, O1/AFz, Fz, CPz, Cz, POz, Pz/FP2, F4, F8, T8, C4, P4, P8, O2) repeated measures ANOVAs on each ERP and assessment session separately. For deviant stimuli, Group × Laterality × Deviant repeated measures ANOVAs will be conducted.

For all amplitude analysis, normality will be assessed by Shapiro–Wilk test. In case of non-parametric distribution of the data, a transformation will be applied. Mauchly’s test of sphericity will be used to evaluate homogeneity of variances and co-variances. In case of violation of sphericity, a Greenhouse-Geisser correction will be applied in order to test main effects significance. *Post hoc* comparisons will be conducted to assess specific differences (Tukey procedure).

All statistical analysis will be performed with R software. Level of significance will be set at *p* < 0.05.

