##### Intervention

Autistic and TD participants involved in this study will have to meet the same criteria than those described in Stage 2. However, participants from Stage 2 will not be included in Stage 3 in order to avoid any bias elicited by a former exposition to the synthetic voices under study.

Sample size estimation was calculated with G^∗^Power software version 3.1.9.7 (Faul et al., 2007) for Cohen’s d effect size index of 0.8, correlations among repeated measures of 0.5, and statistical significance set at *p* < 0.05. For ERP analysis, results indicated that 13 participants in each group would be enough to provide an estimated power of 0.92 for group comparisons, and 11 participants in each group would be enough to provide an estimated power of 0.91 for assessment sessions comparisons. For behavioral analysis on reaction times, results indicated that 13 participants in each group would be enough to provide an estimated power of 0.91 and seven participants in each group would be enough to provide an estimated power of 0.93 for assessment sessions comparisons. For behavioral analysis on number of correct/incorrect answers, results indicated that 18 participants in each group would be enough to provide an estimated power of 0.92 for group comparisons, and 15 participants in each group would be enough to provide an estimated power of 0.90 for assessment sessions comparisons (Cohen’s d effect size index of 0.8, statistical significance set at *p* < 0.05). For behavioral analysis on ASRS scores, results indicated that 16 participants in each group would be enough to provide an estimated power of 0.92 and 18 participants in each group would be enough to provide an estimated power of 0.90 for assessment sessions comparisons.

A total of 72 participants will take part to this Stage and will be divided in four groups:

•Group 1: autistic children receiving robot, synthesized and human voices intervention (18 participants).•Group 2: autistic children receiving robot and human voice intervention (18 participants).•Group 3: autistic children without receiving intervention (18 participants).•Group 4: TD children without receiving intervention (18 participants).

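### In the Stage 3 within-group time ANOVAs, the Mauchly-then-Greenhouse-Geisser rule cannot be run for the interactions that involve ROI, and it leaves them uncorrected as worded

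*Protocol article*

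**What the plan says.** Stage 3, ‘Statistical analysis on ERPs data’, defines three families of ANOVA: group comparisons, time comparisons and scalp distribution (laterality). For standard stimuli the time comparison is Session × ROI, run for each ERP and each group separately. The next sentence adds: "For deviant stimuli, Assessment Session × ROI × Deviant repeated measures ANOVAs will be performed".

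One sphericity rule covers all amplitude analyses. Mauchly's test comes first, and then: "In case of violation of sphericity, a Greenhouse-Geisser correction will be applied in order to test main effects significance". Nothing is said about correcting interactions, or about a term for which Mauchly's test cannot be calculated.

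The inputs are fixed elsewhere in the article:
- ROIs: Stage 3 reuses the Stage 2 list (‘ERPs’: "electrodes will be grouped according to ROIs described in section").
- Sessions: EEG is recorded at five time points (‘EEG assessments’: before, mid and end of intervention, and 2 and 6 weeks after it).
- Deviants: five ("occasional 48 anger (4%), 48 disgust (4%), 48 fear (4%), 48 happiness (4%), and 48 sadness (4%) deviant stimuli").
- Children: four groups of 18 (‘Intervention’, under Participants).

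**The concern.** Mauchly's test uses the determinant of the sample covariance matrix of a term's orthonormal contrasts. When there are more contrasts than error degrees of freedom, that matrix is singular and the test does not exist. An 18-level ROI factor crossed with five sessions and five deviants, analysed in 18 children, passes that limit by a wide margin.

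The correction is triggered only by this test and is worded for main effects. An analyst who follows the text therefore has no trigger for the ROI interactions and would report uncorrected F tests. Neighbouring scalp sites and successive sessions are unlikely to satisfy sphericity, so such tests would be too liberal. If the analyst applies Greenhouse-Geisser regardless, the estimated epsilon is capped far below any plausible true value for the three-way term, and the test becomes very conservative.

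At stake are the terms that show whether a change over sessions differs by scalp region, overall or by emotion. The Discussion names neuronal plasticity after the intervention as an aim.

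**Working it through.** **1. The plan's own figures.** The sample-size text gives power 0.91 for ERP session comparisons with 11 children per group and 0.92 for group comparisons with 13 per group (d = 0.8, correlation 0.5). Take f = d/2 = 0.4.
- Session: λ = n·m·f²/(1−ρ) = 11 × 5 × 0.16/0.5 = 17.6 with 4 and 40 df, epsilon = 1. Power is 0.905.
- Group, N = 52: λ = N·m·f²/(1+(m−1)ρ). With m = 18, 149.76/9.5 = 15.8 gives 0.908. With m = 90 (18 ROIs × 5 deviants), 748.8/45.5 = 16.5 gives 0.920.

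Both figures reproduce. The session figure is for a five-level main effect with sphericity assumed. It does not address the ROI interactions.

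**2. ROI count** (Stage 2, ‘Data Analysis’): FP1; F3/F7; FP2; AFz; Fz; F4/F8; T7; C3; Cz; T8; C4; CPz; P3/P7; Pz; P4/P8; POz; O1; O2. That is 18 levels, so 17 contrasts.

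**3. Contrasts against error df in a one-group time ANOVA** (18 − 1 = 17):

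| Term | Contrasts | Mauchly's test exists? |
|---|---|---|
| Session | 4 | yes |
| Deviant | 4 | yes |
| Session × Deviant | 4 × 4 = 16 | yes |
| ROI | 17 | only with all 18 children (one loss leaves 16 df) |
| Session × ROI | 4 × 17 = 68 | no |
| ROI × Deviant | 17 × 4 = 68 | no |
| Session × ROI × Deviant | 4 × 17 × 4 = 272 | no |

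The test would need 69 children per group for the two-way ROI terms and 273 for the three-way term.

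The group and laterality ANOVAs pool 72 children in four groups: error df 72 − 4 = 68. ROI (17), ROI × Deviant (68, none to spare), Laterality (2) and Laterality × Deviant (8) are all computable there.

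**4. Does the ROI screen help?** One-sample t-tests precede the ANOVAs and might reduce the ROIs to r.
- Session × ROI needs 4(r − 1) ≤ 17, so r ≤ 5.
- The three-way term needs 16(r − 1) ≤ 17, so r ≤ 2.

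**5. Ceiling on the Greenhouse-Geisser epsilon.** A covariance estimate of rank at most 17 gives epsilon ≤ 17/68 = 0.25 for the two-way ROI terms and ≤ 17/272 = 0.0625 for the three-way term.

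**6. Error rates under the null, nominal 0.05.** The documents give no covariance, so these are assumptions: correlation falling with distance over the 18 ROIs (three forms), AR(1) 0.7 over sessions, equal correlation over deviants, plus a spherical reference. There were 1,200 to 4,000 runs per term.

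| Covariance (true epsilon) | Session × ROI: uncorrected / GG | Three-way: uncorrected / GG |
|---|---|---|
| Spherical (1.000) | 0.047 / 0.000 | 0.048 / 0.000 |
| Length 0.5 (0.482) | 0.116 / 0.005 | 0.122 / 0.000 |
| Length 1.0 (0.344) | 0.145 / 0.010 | 0.154 / 0.000 |
| Length 1, smooth (0.195) | 0.196 / 0.025 | 0.208 / 0.001 |

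The mean estimated epsilon in the three non-spherical settings was 0.110 to 0.163 for Session × ROI and 0.047 to 0.055 for the three-way term, well below the true values. Further runs with correlation lengths of 0.5 to 2 head radii agreed in direction, with uncorrected rates starting at 8%. Over all runs the ranges are about 8–21% uncorrected and 0–2.5% with Greenhouse-Geisser. No rate was simulated for ROI × Deviant; for that term the point rests on the contrast count.

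**7. Terms outside this point, same settings.** The two-stage rule gives 0.048–0.056 for the Session main effect and 0.040–0.047 for Group × ROI.

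**The case against.** **This is a condensed article, and an analysis plan may fill the gap.** That would answer an omission. Here the article states the rule and every count it depends on, and the stated rule cannot be carried out for these terms. It is fair that the article is silent on correcting interactions, so uncorrected tests are the consequence of its wording and not a declared choice.

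**The deviant sentence does not itself say that the analysis is per group.** True; it is read with the sentence before it. The standard-stimulus Session × ROI ANOVA is explicitly per group, so 68 contrasts against 17 df stands either way. Even with all 72 children pooled (68 error df), the three-way term's 272 contrasts would exceed the limit.

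**The ROI screen may shrink the factor.** It may, but only five or fewer surviving ROIs (two or fewer for the three-way term) would make the test computable.

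Several stronger readings are tempting and are not supported:
- *The rule fails for all Stage 3 ERP ANOVAs.* The group and laterality families have 68 error df, and every term there is computable.
- *Both branches always give wrong error rates.* The rule holds near 5% for the Session main effect, and the uncorrected F is correct if sphericity holds.
- *Change over sessions by emotion cannot be tested.* That is Session × Deviant: 16 contrasts against 17 df.
- *Greenhouse-Geisser removes almost all power.* Null rejection rates do not show this. Power depends on effect size and covariance, and the documents give neither for these interactions. In one simulation of the three-way term, corrected power was 1–25% for a 0.4 SD change but at least 95% for a 0.8 SD change.

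**Conclusion.** The point holds for the ROI terms of the within-group time ANOVAs. Mauchly's test does not exist for Session × ROI, ROI × Deviant or Session × ROI × Deviant, and it exists for ROI only with complete data from all 18 children. The Discussion itself expects that withdrawals could be frequent.

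As worded, the three interactions would go uncorrected. For Session × ROI and the three-way term that means about 8–21% false positives instead of 5%. Greenhouse-Geisser used regardless gives about 0–2.5%.

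The contrast counts and epsilon ceilings follow from the document alone. The error rates depend on assumed covariances, so their direction is firmer than their exact size.

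**What to change.** For the time comparisons, replace the 18-level ROI factor with one pre-stated region per component. The article's section ‘EEG Signature of Emotion Recognition’ already points to fronto-central sites for MMN and P3a and centro-parietal sites for LPP. A region for P200 must be stated as well.

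On each regional average, test Session, Deviant and Session × Deviant in one of two ways:
- repeated measures ANOVA with a sphericity correction applied to every within-subject term, without a Mauchly pre-test; or
- a mixed model with child, child-by-session and child-by-deviant random effects and small-sample degrees of freedom. A random intercept alone would assume sphericity again.

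With 16 contrasts on 17 df, Greenhouse-Geisser remains conservative for Session × Deviant (0.011–0.026 in the simulations above), which favours the mixed model.

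Test the ROI interactions by permutation and label them exploratory.

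The change needs no extra children, visits or recordings. It costs topographic detail in the main tests, and the ERP power statement must be tied to the new model.

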
#### Outcome Measures

##### ASRS questionnaire

The ASRS questionnaire is a standardized, reliable and validated set of questions targeted to parents or teachers of autistic people aged between 2 and 18 years to measure their autistic symptomatology (Simek and Wahlberg, 2011). It presents several advantages for its use in research (Goldstein, 2012). First, a wide range of autistic social and emotional behaviors are assessed, so that it makes the evaluation of generalization of learning to other social domains possible. Second, the scores provided are based on a normative TD sample, thus it considers the autism spectrum as a continuum with the general population making possible the comparison with a TD control group. The full-length version for 6–18 years old children and youths is composed of 71 items divided in three scales: ASRS scale, DSM-IV, and Treatment Scale. A 4-level scale is presented to the rater in order him to specify how often a particular behavior is used to be observed in the child or youth that is evaluated. Higher scores indicate higher symptoms severity according to the rater. In this study, a particular focus will be dedicated to Social/Communication, DSM-IV-TR, Peer and Adult Socialization and Social/Emotional Reciprocity domains. Parents of both groups will answer this questionnaire on pre-intervention (1st session) and follow-up sessions (2 and 6 weeks after the end of the intervention).

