##### Behavioral assessments

At pre- (1st session), mid- (7th session), end- (13rd session), and follow-up sessions (2 and 6 weeks after the end of the intervention), participants will be asked to answer the following behavioral task. It will consist of one block of stimulus pairs containing 244 pairs that will be presented at 60 dB via the Shure SRH1840 audio headset. The stimulus pair will be composed of either identical stimuli (50%; two neutral stimuli), or different stimuli [one neutral and one of the emotional deviants (50%; anger (10%), disgust (10%), fear (10%), happiness (10%), or sadness (10%)]. Fifty percent of pairs that contain a deviant stimulus will be composed of 1 neutral followed by 1 emotional stimulus, and 50% will be composed of 1 emotional followed by 1 neutral stimulus. Word pairs will be equally uttered with a male, woman, or child voice. The within-pair stimulus onset asynchrony will be 1,300 ms, and the between-pair stimulus onset asynchrony will be 2,600 ms. The order of stimulus pairs will be randomized between participants, but the stimulus sequence will be fixed. During this approximately 20-min task, participants will have to answer by pressing previously instructed keys on a laptop keyboard, if the emotional prosody of both stimuli of each pair will be the same or different. If they choose different, they will have to mention the emotion conveyed by the deviant (anger, disgust, fear, happiness, or sadness). Reaction times and correct/incorrect answers will be recorded. To make sure that the participant understands the task, three training trials will be presented before the test. Autistic participants will be accompanied by their parent if necessary.

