#### Data Analysis

##### Statistical analysis on ASRS scores

Group comparisons will be conducted by one-way ANOVAs on T-scores for each assessment session and symptom domain (Social/Communication, DSM-IV-TR, Peer and Adult Socialization, and Social/Emotional Reciprocity) separately.

Time comparisons (between assessment sessions) will be tested by one-way ANOVAs on T-scores for each group and symptom domain (Social/Communication, DSM-IV-TR, Peer and Adult Socialization and Social/Emotional Reciprocity) separately.

Normality and homogeneity of variances will be assessed by Shapiro-Wilk and Bartlett tests, respectively. In case of non-parametric distribution of the data, Kruskal-Wallis test will be applied. Post-hoc comparisons will be conducted to assess specific differences (Tukey procedure in case of ANOVA, Wilcoxon tests with *p*-value adjustment by Holm method in case of Kruskal–Wallis test).

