##### Statistical analysis on behavioral data

Group comparisons of reaction times will be conducted by a Group × Stimulus (neutral, anger, disgust, fear, happiness, or sadness) repeated measures ANOVAs on each assessment session separately. Time comparisons will be conducted by Assessment Session × Stimulus on each group separately. Normality of reaction times will be assessed by Shapiro–Wilk test. In case of non-parametric distribution of the data, a transformation will be applied. Mauchly’s test of sphericity will be used to evaluate homogeneity of variances and co-variances. In case of violation of sphericity, a Greenhouse-Geisser correction will be applied in order to test main effects significance. Post-hoc comparisons will be conducted to assess specific differences (Tukey procedure).

Group comparisons of number of correct answers will be conducted by one-way ANOVAs for each deviant and assessment session separately. Time comparisons (between assessment sessions) will be tested by one-way ANOVAs on number of correct answers for each deviant and each group separately. Normality and homogeneity of variances will be assessed by Shapiro–Wilk and Bartlett tests, respectively. In case of non-parametric distribution of the data, Kruskal–Wallis test will be applied. *Post hoc* comparisons will be conducted to assess specific differences (Tukey after ANOVA, Wilcoxon tests with *p*-value adjustment by Holm method after Kruskal–Wallis).

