Group 1 will be the experimental group and groups 2–4 will be controls. Children from group 2 will receive the same intervention as children from group 1, with the exception of the use of human voices only. This group will help to evaluate the efficacy of the use of synthesized voices in the intervention. Autistic participants will be randomly assigned to any of groups 1, 2 or 3. All four groups will be included in pre-, mid-, end and follow-up assessments.

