This project of investigation might encounter some pitfalls and unexpected results. Non-professionalism of actors recruited for emotional recordings during Stage 1 may affect the reliability of required prosodies. Nevertheless, the number of volunteers will be increased in order to generate four times more utterances than necessary to enable the selection of best actor participants. Furthermore, emotion recognition accuracy will be validated by supervised learning algorithm to ensure the quality of emotion discrimination based on acoustic features. Stage 2 aims to explore emotional recognition impairments in autism triggered by naturalness of human voices. We expect to observe a diminution of the amplitude of ERPs in the autistic population as a reflect of decreased attentional, sensorial, and cognitive emotional processing (Lartseva et al., 2015; Lindström et al., 2016, 2018). The autistic condition may also be characterized by hemispheric lateralization anomalies due to lateralized compensatory brain activity (Subbaraju et al., 2018). Impairments are expected to fade with the decreasing naturalness of voice stimuli. However, in the opposite case, no effect of naturalness on neural emotional processing by autistic children would be an evidence that the modulated acoustic parameters would not participate to autistic impairments. In the latter situation, or in case of enhancement of autistic impairments triggered by naturalness modulations, the acoustic edition of the stimuli will be reconsidered. Finally, Stage 3 expects the implementation of less natural voices in a robot-based intervention with the aim of improving emotion detection by autistic children. The 2-week intervention may imply a high rate of withdrawals whereas the sample size needed is relatively high. However, upon completion, we expect the intervention to trigger a reduction of autistic impairments (reduction of symptomatology, higher EEG activity, higher behavioral accuracy for emotion discrimination: smaller reaction times, and higher correct answers at end- and follow-up assessments).

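### Stage 3 names no primary test, so the key Group 1 vs Group 2 comparison recurs as a post hoc pair in about 64 post-baseline tests with no correction across them

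*Protocol article*

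**What the plan says.** **Groups.** The Intervention paragraph under Stage 3 Participants states "A total of 72 participants will take part to this Stage and will be divided in four groups", with 18 children in each. Three groups are randomised autistic groups and the fourth is typically developed (TD). Then: "Group 1 will be the experimental group and groups 2–4 will be controls". Group 2 gets the same intervention with human voices only, and is there to show what the synthesized voices add. The Conclusion gives testing the efficacy of less natural voices as the aim of this stage.

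**Assessments.** For the ASRS: "Parents of both groups will answer this questionnaire on pre-intervention (1st session) and follow-up sessions (2 and 6 weeks" after the intervention), so three sessions. For the behavioural task and EEG: "At pre- (1st session), mid- (7th session), end- (13rd session), and follow-up sessions (2 and 6 weeks after the end of the intervention"), so five sessions.

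**Tests.**
- ASRS: "Group comparisons will be conducted by one-way ANOVAs on T-scores for each assessment session and symptom domain", plus time comparisons for each group and domain.
- Correct answers: "Group comparisons of number of correct answers will be conducted by one-way ANOVAs for each deviant and assessment session separately", plus time comparisons for each deviant and group.
- Reaction times: one Group × Stimulus ANOVA per session and one Session × Stimulus ANOVA per group.
- ERPs: group, time and laterality ANOVAs for four components, for standard and deviant stimuli separately, restricted to components that pass one-sample t-tests against zero.

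**Error rule.** The section on ERPs data ends the Stage 3 analysis with "All statistical analysis will be performed with R software. Level of significance will be set at" p < 0.05, so every test is at that level. Tukey, or Holm after Kruskal–Wallis, is applied to the post hoc pairs of one ANOVA at a time.

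**Expected result.** The Discussion says "we expect the intervention to trigger a reduction of autistic impairments", and lists symptoms, EEG activity, reaction times and correct answers at the end and follow-up assessments.

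**The concern.** Outcome Measures lists three kinds of outcome and ranks none. The sample-size paragraph treats ERPs, reaction times, correct answers and ASRS side by side, and three different groups serve as controls. The question the randomisation is built to answer is whether adding the synthesized voice helps, that is, Group 1 vs Group 2. That contrast has no test of its own. It is one of six pairs in each four-group ANOVA, repeated over outcomes, deviants and sessions.

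The within-ANOVA correction limits error over those six pairs. It does nothing about the repetition. One significant Group 1 vs Group 2 pair out of dozens could then be reported as evidence for the synthesized voice, and the plan has no rule for judging how surprising it is.

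**Working it through.** **1. The plan's own figure.** The article states no overall error rate to reproduce. Its nearest figure is power of 0.92 at 18 per group for the group comparison of correct answers. A noncentral-F calculation with 4 × 18 children and f = d/2 = 0.4 gives 0.80. The same formula does reproduce the Stage 1 figures (6 × 19: 0.916 against 0.92; 2 × 34: 0.90 against 0.90). That mismatch is a separate matter and nothing below depends on it.

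**2. Count of ANOVAs as written.**

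| Outcome | Group tests | Time tests | Laterality |
|---|---|---|---|
| ASRS | 4 domains × 3 sessions = 12 | 4 domains × 4 groups = 16 | – |
| Reaction time | 5 sessions = 5 | 4 groups = 4 | – |
| Correct answers | 5 deviants × 5 sessions = 25 | 5 deviants × 4 groups = 20 | – |
| ERPs | 4 ERPs × 5 sessions × 2 stimulus types = 40 | 4 ERPs × 4 groups × 2 = 32 | 4 ERPs × 5 sessions × 2 = 40 |

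Total: 12 + 16 + 5 + 4 + 25 + 20 + 40 + 32 + 40 = 194. The 112 ERP ANOVAs are a maximum, because components that fail the t-tests drop out.

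**3. Tests that carry Group 1 vs Group 2 after baseline.** Remove:
- the pre-intervention group tests: ASRS 4 + reaction time 1 + correct answers 5 + ERP 8 + laterality 8 = 26;
- the time tests in untreated Groups 3 and 4: 8 + 2 + 10 + 16 = 36;
- the post-baseline laterality tests: 32;
- the time tests within Groups 1 and 2: 36.

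194 − 26 − 36 − 32 − 36 = 64, made up of ASRS 8, reaction time 4, correct answers 20 and ERP 32.

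**4. Error of one pair.** For Tukey with four groups of 18 (68 residual degrees of freedom) the 5% studentized-range point is 3.725. The pair is called different if |t| > 3.725/√2 = 2.634, a two-sided per-pair error of 0.0104.

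**5. Chance of at least one false Group 1 vs Group 2 difference.** If independent, this is 1 − (1 − 0.0104)^m:

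| Set | m | Chance |
|---|---|---|
| Reaction time | 4 | 4% |
| ASRS | 8 | 8% |
| Correct answers | 20 | 19% |
| ERP | 32 | 29% |
| All | 64 | 49% |

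Tests on the same children are correlated. I simulated four groups of 18 with no group difference, equal correlation among a child's 64 measures and one Tukey pair per measure:

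| Assumed correlation | Chance over 64 tests |
|---|---|
| 0 | 49% |
| 0.3 | 37% |
| 0.5 (the article's repeated-measures value) | 26% |
| 0.7 | 14% |
| 0.9 | 6% |

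Repeat runs differ by about one percentage point. The expected number of false pairs is 64 × 0.0104 = 0.67 at any correlation.

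**6. Sensitivity.** Dropping the mid-intervention session, because the Discussion speaks of end and follow-up, leaves 8 + 3 + 15 + 24 = 50 tests. Then 1 − (1 − 0.0104)^50 = 41% if independent.

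**7. Power of a single Group 1 vs Group 2 test.** With 18 per group and d = 0.8, the noncentrality is 0.8 × √(18/2) = 2.4 on 34 degrees of freedom, and power is 0.65. Adjusting for a pre-intervention score with r = 0.5 (assumed) gives 0.8/√(1 − 0.25) = 0.924, noncentrality 2.77 on 33 degrees of freedom, and power 0.77.

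**The case against.** A reader might go further and say that 194 tests at 5% make a positive result near certain: 194 × 0.05 = 9.7 false positives and 1 − 0.95^194 above 0.999. The documents do not support that as an efficacy error rate, for four reasons.

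- Many of the 194 tests are pre-intervention comparisons, time tests in untreated groups or laterality tests, and the ERP share is a ceiling.
- A four-group omnibus test does not show that Group 1 differs from Group 2.
- For the ASRS the four-group null is false by design. Autistic children enter with T-scores above 60 on the named domains and TD children below 60, so a baseline rejection reflects selection and is not a false positive. EEG differences from TD children are expected too.
- Tukey does protect each pair, at 0.0104 rather than 0.05.

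Nor does the article say that any significant cell counts as success. It gives an expected direction, names end and follow-up, and says what Group 2 is for.

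It can also be argued that a hierarchy belongs in a full protocol, analysis plan or registration that is not shown. That is fair as to the missing ranking, and a registration is cited whose content cannot be checked here. It does not dispose of the point: the article itself fixes the tests, how they are split, the level for each and the scope of the corrections. Followed as printed, that rule inflates the error on the central contrast.

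**Conclusion.** The point holds in this form. Stage 3 as described has no primary outcome, time point or contrast, and controls error only within each of up to 194 ANOVAs. For Group 1 vs Group 2 over the 64 post-baseline group tests, the chance of at least one false difference is about 26% at the article's own correlation of 0.5. It ranges from 49% if independent to 14% at 0.7, and nears the nominal 5% only at about 0.9.

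These figures assume one Tukey pair on the Group effect per test, equal correlation among a child's measures, and all ERP components retained. Interaction contrasts in the factorial ANOVAs are not counted. Under the Holm fallback, if the three TD pairs are rejected first, the smallest remaining pair is judged at 0.05/3 = 0.0167, so the Tukey figures are not an upper limit.

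This should be corrected before the analysis. It does not show that the trial cannot detect an effect.

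**What to change.** 1. Name one primary outcome, one time point and the Group 1 vs Group 2 contrast, adjusted for the pre-intervention score and tested at 0.05. Total correct answers over all deviants at the end assessment is one example; the choice is the sponsor's. If the registration already names a primary outcome, carry it into the plan.
2. Make the remaining post-baseline comparisons secondary, with Holm across all tests within each outcome family (ASRS, behavioural, ERP).
3. Label per-deviant, per-ROI, laterality and within-group time analyses exploratory.
4. State the power of the primary contrast.

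The change is to wording and needs no new data. It has two costs. Fewer results can be called confirmatory. And the power for this contrast at 18 per group and d = 0.8 must be given as about 0.65 unadjusted, or about 0.77 with baseline adjustment if r = 0.5, below the 0.90–0.93 the sample-size paragraph quotes for its Stage 3 analyses.
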